### Sample size

Variability was estimated from the feasibility study.
^24^ Estimates of the standard deviation (SD) for systolic BP change from baseline at 4-weeks, 3 and 6-months were 12.5, 10.8 and 14.4 mmHg respectively. With a minimal clinical important difference 5 mmHg and SD of 14.4, we require 352 participants to complete this study to attain 90% power with a 5% significance level. Assuming 35% attrition we aim to randomise 542 participants, 271 in each group. The sample size confidence interval has been calculated using Pass11 software (PASS 11. NCSS, LLC. Kaysville, Utah, USA.
www.ncss.com).

For qualitative data samples, we will conduct up to four online focus groups of 6–8 participants each from the intervention group plus up to 15 interviews with stakeholders – it is expected that this sample will achieve data saturation whereby no new qualitative data codes/elements are identified when approaching the full sample.
^25^

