Standard care lifestyle advice consists of National Institute for Health and Care Excellence (NICE) guidance with or without a single antihypertensive agent (excluding beta-blockers due to impact on heart rate and possible attenuation of the benefit of IE).
^1^ Standard care advice will be provided in the online study portal and by email to all participants as a video summary and signposting to the BPUK “How to Lower Your Blood Pressure” webpage.
^27^

**
*Isometric Exercise Training – intervention arm only*
**

The intervention will be self-delivered by participants using the instruction materials provided (videos) within the website portal and written instructions (downloadable or by email/post if requested). Participants will be taught how to perform an isometric exercise wall squat (
Figure 1)
^28^ that is tailored to their own optimum intensity that should be conducted for four bouts of two minutes each in the appropriate squat position. Two minutes rest will be completed in between each bout.
^21–30^ This will be performed three times a week for the duration of the study a total of 6-months (or 12-months for a sub-group of n = 50).

Personalisation of the exercise plan is achieved in the first session by establishing an individualised optimum intensity
^31^ based on a rating of perceived exertion (RPE) for isometric exercise scale (
Figure 3).
^32^
^,^
^33^ The isometric wall squat protocol employed uses RPE to determine the correct individualised wall squat height/knee joint angle to elicit the necessary level of cardiovascular stress proven to result in longer term resting blood pressure reduction/adaptation.
^31^
^,^
^32^ The progressive RPE training zones used to inform the four bouts that make up each isometric exercise session have been determined to replicate a warm up period and achieve a target heart rate and blood pressure previously documented when using the originally validated wall squat protocol based upon 95% HRpeak as measured during an incremental isometric exercise test.
^20^
^,^
^21^

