Participants will receive electronic reminders (email, text or WhatsApp message depending on participant preference) ahead of each follow up time point to prompt data collection. They will receive further reminders on the day of assessment and then daily during the submission window (refer to above) to submit their information through the online questionnaire. Intervention arm participants will receive reminders of exercise sessions as per their preferences set during baseline data collection. Weekly motivational messages will also be sent to control participants for the first 6 weeks of the study. This will aid adherence to the study and IE training and reminders will include a link to input their data each time or at regular weekly intervals. At each follow up, participants will record their home blood pressure, heart rate readings and in their participant diary and submit these via an online questionnaire using a link emailed or texted to participants. Alternative methods for data recording will be made available to participants where requested, for accessibility (telephone call, on paper etc.) and supported by local teams or the study team centrally.

The protocol requires three consecutive measurements (separated by two minutes) always using the same arm (use arm with high reading if >15 mmHg difference when first checked), to be taken in the morning and afternoon for three days at each timepoint. Home blood pressure monitoring will follow NICE and ESH/ESC guidelines
^1^
^,^
^26^ using a British and Irish Hypertension Society approved blood pressure monitor. Participants will be asked to keep their chosen times of blood pressure measurements and ingestion of medication consistent throughout the study. Adverse events, checking of medication, adapted version of UK EPIC NORFOLK Food Frequency Questionnaire,
^34^ General Practice Physical Activity Questionnaire,
^35^ EuroQOL quality of life 5D-5L questionnaire,
^36^ study-specific IE intervention experience questionnaire (intervention group only at week 4) and health economics data (questionnaire adapted for the study from
^37^) will also be collected according to the schedule of assessments (

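### Between-assessment contact becomes more unequal after week 6, because the control arm's weekly messages stop before the 3-month primary endpoint while exercise reminders have no stated end

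*Protocol article*

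**What the plan says.** All of the contact schedule is in the protocol article, under Participant on study timeline and assessments (follow-up assessments).

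- **Both arms, tied to assessments.** Everyone receives reminders "ahead of each follow up time point to prompt data collection". In addition, "They will receive further reminders on the day of assessment and then daily during the submission window".
- **IE arm, between assessments.** "Intervention arm participants will receive reminders of exercise sessions as per their preferences set during baseline data collection". No frequency and no end date are given. Under Participant enrolment, the training is described thus: "This will be performed three times a week for the duration of the study a total of 6-months".
- **Control arm, between assessments.** "Weekly motivational messages will also be sent to control participants for the first 6 weeks of the study".
- **Stated purpose.** The next sentence reads "This will aid adherence to the study and IE training and reminders will include a link to input their data", with the link given at each reminder or weekly.

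The Sample size section plans for heavy loss: "Assuming 35% attrition we aim to randomise 542 participants, 271 in each group". The primary outcome is the change in home systolic BP at 3 months. Four weeks and 6 months are secondary time points.

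**The concern.** Controls have no exercise training to adhere to. For them, the only purpose the protocol gives for the weekly messages is to keep them in the study. That tool is withdrawn at week 6, which matches no assessment (Day 30, Month 3, Month 6), and the article gives no reason for the cut-off. Up to week 6 both arms have some regular contact between assessments. Afterwards only the IE arm has any, if its reminders run as long as its training.

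The trial is unblinded and remote, and relies on BP readings that participants submit themselves. If controls who hear nothing between assessments stop replying more often than IE participants, and those who stop differ in later BP, the comparison at months 3 and 6 could be distorted. The planned imputation model draws on baseline covariates and week-4 BP, all measured before contact diverges. It cannot correct for later differences that those variables do not predict.

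**Working it through.** **1. The plan's own figure.** Inputs from Sample size: difference 5 mmHg, SD 14.4 mmHg, 90% power, 5% significance (two-sided, from Statistical methods).

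- Normal approximation: n per arm = 2 × (1.960 + 1.282)² × 14.4² / 5² ≈ 174.3, so 175 per arm.
- Two-sample t-test version: 176 per arm, 352 in total, as stated.
- Inflation for loss: 352 / (1 − 0.35) = 541.5, so 542, as stated.

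The sample size is sound and does not depend on the contact schedule.

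**2. Contact between assessments.** Taking 3 months as 13 weeks and 6 months as 26:

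- Control messages cover 6/13 = 46% of the time to month 3 and 6/26 = 23% of the time to month 6.
- The period without them is 13 − 6 = 7 weeks before month 3 and 26 − 6 = 20 weeks before month 6.
- IE reminders, if there were one per planned session (an upper figure, since frequency follows preference): 7 × 3 = 21 in weeks 7–13 and 20 × 3 = 60 in weeks 7–26. The control count in both periods is 0.

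**3. Effect on power.** The document gives no loss by arm, so the splits below are assumptions that hold the overall loss at 35% of 271 per arm.

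| Loss IE / control | Completers IE / control | Power, SD 14.4 | Power, SD 10.8 |
|---|---|---|---|
| 35% / 35% | 176.2 / 176.2 | 0.903 | 0.991 |
| 30% / 40% | 189.7 / 162.6 | 0.901 | 0.991 |
| 25% / 45% | 203.2 / 149.1 | 0.896 | 0.990 |
| 20% / 50% | 216.8 / 135.5 | 0.887 | 0.988 |

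Power barely moves. Any harm would come through bias.

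**4. Illustrative bias in a completer analysis.** Let D be the mean change among those lost minus that among those retained, assumed equal in both arms. In each arm the completer mean equals the full mean minus (loss × D). The IE-minus-control contrast is therefore shifted by (loss in control − loss in IE) × D.

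| Gap in loss | D = 2 mmHg | D = 5 mmHg | D = 8 mmHg |
|---|---|---|---|
| 0 points | 0 | 0 | 0 |
| 10 points | 0.2 | 0.5 | 0.8 |
| 20 points | 0.4 | 1.0 | 1.6 |
| 30 points | 0.6 | 1.5 | 2.4 |

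If controls are lost more often and those lost do worse, the shift understates the benefit of exercise. Reversing either assumption reverses the sign. For scale, the standard error of the difference with 176 per arm is SD × √(2/176): 1.15 mmHg at SD 10.8 and 1.54 mmHg at SD 14.4.

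**The case against.** The case for leaving the schedule alone is substantial, and most of it stands.

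- **Contact at the assessments is matched.** The prompts that secure a BP submission are the same in both arms at week 4, month 3 and month 6. A reader might infer that controls are out of contact at the primary endpoint. The text does not support that, because only contact between assessments differs.
- **Week 4 is not a clean baseline of equal contact.** Controls get one message a week, and IE participants may get up to three reminders. Contact is similar at best, so a reader should not treat week-4 results as obtained under equal contact.
- **Continued IE reminders are inferred.** The article gives no duration for them. The inference rests on the 6-month training programme.
- **The data-entry link may serve exercise data.** No BP is due between assessments, so the link is not shown to give the IE arm an extra route for submitting BP.
- **Retention and missing data are addressed.** Controls are offered the exercise programme at the end as a reason to stay, and all participants keep their BP monitor. Statistical methods plans a pattern-mixture sensitivity analysis if missingness appears related to allocation. A reader might infer that the plan ignores uneven loss, but it does not. That analysis is conditional, however, and examines the consequence after data are lost.
- **The direction is unknown.** Three sessions a week for 6 months could instead drive more loss in the IE arm.
- **The mmHg figures do not describe the planned analysis.** At 35% loss, multiple imputation would be used (the band is 5% to 40%), and the figures apply to completers.
- **Contact need not be matched.** Session reminders are arguably part of the intervention, and a standard-care comparator need not mirror them.

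What remains is that, by the protocol's own rationale, a retention aid for controls ends about 7 weeks before the primary endpoint, without explanation.

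**Conclusion.** The point holds as a foreseeable risk of differential attrition that is cheap to reduce. It is not an error in the analysis or in the sample size. The article fixes the 6-week cut-off expressly, so this is not a detail left to another document. The claim that the gap widens after week 6 assumes that IE reminders continue for as long as the training does.

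The size of any bias cannot be derived from the document. The 0.2 to 2.4 mmHg range, against a 5 mmHg target, rests on assumed gaps in loss of 10 to 30 points and assumed differences of 2 to 8 mmHg between those lost and those retained. It should not be read as an estimate of bias in this trial.

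**What to change.** In the follow-up part of Participant on study timeline and assessments, continue the automated weekly messages to controls through the Month 6 assessment. After week 6, limit them to neutral retention content: thanks, the date of the next readings, and a link to the participant portal. Leave the IE session reminders as they are.

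**Cost.** About 26 − 6 = 20 further automated messages per control participant, sent through the messaging already in use, and a minor amendment. The downside is slightly more contact than usual care, which neutral content keeps small.

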### Statistical methods

The primary outcome will be to assess a change from baseline home average systolic BP (mmHg) in the IE intervention arm compared to control arm at 3-months. The secondary outcomes to be evaluated at 4-weeks, 3-months, 6-months include:
•proportion of participants with home average BP of ≤135/85 mmHg compared to baseline;•prescription changes from baseline to timepoints using anti-hypertensive treatment intensity score
^40^;•home average Systolic BP at 4-weeks, 6-months in IE vs Control and 12-months in IE;•home average Diastolic BP at 4-weeks, 3-months, 6-months in IE vs. control and 12-months in IE;•evidence the fidelity of the study intervention when it is self-prescribed (RPE recorded in range at the last bout for the first week of training) from a subset of the first 50 participants in intervention arm;•understand participant experiences of ability to take up, self-administer and conduct the IE programme, including barriers and facilitators for long term adherence;•changes in the use and costs from a UK NHS and personal social services perspective in both groups at 3-months and 6-months; changes in the QOL in both groups at 3-months and 6-months;•total cost of the intervention and cost per participant; cost consequence analysis of the intervention including QALYs in both groups at 3-months and 6-months;•to evaluate other changes in lifestyle because of uptake of IE as a lifestyle measure at 3 months, 6 months and 12 months in IE.

The study was powered to detect a 5 mmHg difference which is deemed to be representative of the minimal clinical important difference. A subset (n = 50) of participants will be followed to 12-months where consent is obtained.

Quantitative data analysis.

The primary outcome, change from baseline in systolic BP at 3-months, will be analysed using analysis of covariance, with a fixed treatment effect allowing adjustments for baseline values, sex, age, and hypertension medication status. The primary analysis will be conducted using an intention to treat approach with a two-sided 5% significance level. Secondary analysis will examine treatment effects under different scenarios for compliance with allocation/treatment, using per protocol approaches. Prior to analysis distributional assumptions will be assessed, and the data may be transformed or alternative nonparametric approaches used where there is evidence of non-normality. Data from the IE experience questionnaires will be analysed using descriptive statistics, as will secondary process outcomes such as recruitment and adherence rates, attrition and completeness of the data.

We will undertake an interim analysis of the first 50 participants’ fourth bout RPE scores and the extent to which these are in range of the target zone to check intervention fidelity to determine the extent to which the intervention is being delivered as intended. Data collected for this purpose involves confirmation from participants on whether they altered their wall squat height and whether their RPE was outside of range.

To avoid loss of efficiency, missing outcome values (both primary systolic blood pressure and secondary diastolic blood pressure) will be imputed using multiple imputation, if the proportion of missing data is greater than 5% and less than 40%.
^41^ Where there are less than 5% missing data, the proportion of missing data is considered negligible and missing observations will be excluded. Multiple imputation methods perform less well when the amount of missing data is substantial, if more than 40% of the primary outcome data are missing in the primary analysis the assumptions are less plausible. The interpretative limitations of the trial data will be discussed in the results section, where this is the case.

An imputation model containing all potential prognostic baseline covariates, the primary outcome variable at 4 weeks follow-up, and the secondary outcome variable diastolic blood pressure at 4 weeks follow-up will be used.
^42^ The number of imputations will be dependent on the amount of missing data, as a minimum the number of imputations will be derived to ensure at least 96% statistical efficiency (RE) according to the formula below, where
*λ* is the fraction of missing values and M is the number of repetitions.
^42^

The statistical model and assumptions made in the analysis of the primary outcome will also be implemented in the multiple imputation procedures. If it is suspected data is missing not at random or the pattern of missing data is associated with trial allocation, sensitivity analysis will be performed using a pattern mixture approach with mixed modelling and multiple imputation
^5^ to compare the sensitivity of conclusions to varying assumptions about the missing value mechanism. All available data from baseline to the time of dropout will be included in the sensitivity analysis using a repeated measures mixed effects model.

A full Data Analysis Plan can be found in our study Data Repository referenced at the end of this manuscript in the Data Availability section.

**
*Qualitative data analysis*
**

Inductive thematic analysis of focus group/interview transcripts will be carried out using NVivo 11. Thematic analysis will be carried out using Braun and Clarke’s (2013) six stage model.
^43^ Drawing on Sweeney
*et al*.’s
^44^ notion that the service user researcher unique perspective should be preserved rather than subsumed, the process will involve multiple members (including public co-applicants) independently (stages 1–3, data familiarisation, initial coding and themes) before joining together to generate a consensus view (stages 4–6, reviewing, defining, naming themes and report production). To guide the thematic analysis of the participant, focus groups, a behaviour change framework (COM-B) has been used to refine the interview questions and will be used to guide analysis.
^45^ For stakeholder interviews, the RE-AIM framework will be used to understand full implementation contexts.
^46^ The findings will be fed back to respondents for validation or revision of the interpretations. Deviant case analysis will be used to ensure that perspectives that diverged from dominant trends are not overlooked.

**
*Health economic analyses*
**

We will conduct a cost consequence analysis and present evidence on a range of costs and outcomes associated with the intervention. We will present the number and percentage of participants with missing values for each cost element and each outcome measure. Data from the QOL and economic questionnaires will be transferred to STATA 18 and analysed using descriptive statistics. We will estimate the mean and 95% confidence intervals for each type of cost (intervention, NHS primary care, NHS secondary care), and the difference between intervention and control group. We will calculate the mean QOL and 95% confidence intervals for both groups both unadjusted and after adjusting for baseline utilities and we will estimate the difference between the two groups. We will also estimate the QALYs for each group at 3-months and 6-months.

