**Figure 3. f3:**
[figure not shown]
Rating of Perceived Exertion (RPE) scale for optimising training intensity.

How high the participant’s back is positioned against the wall affects the perception of exertion when performing an isometric wall squat and this can be used to personalise their back position/squat height for optimum training sessions. Initially, participants perform a 30-second wall squat to locate an approximate height that they estimate would result in a score of 4 on the RPE scale when held for 2-minutes (
Figure 2 – training zone 1) – this will then be marked on the wall using white tack or a marker. Following 2-minutes of seated rest, this is repeated for four bouts of 2-minutes IE with 2-minutes rest in between, feeling harder each time. Each time they will rate their perceived exertion and whether this falls within the correct training zones (
Figure 2 training zones 1–4). If outside the target range, they will be instructed to alter their squat position up or down by 1 cm to achieve target range. At the end of this set of wall squat positions participants will have established and marked the optimum depth of their individual wall squat and will be achieving the appropriate physiological response for clinical benefit.
^31^
^–^
^33^

Intensity is maintained and monitored by RPE ratings during subsequent training sessions. If a participants RPE in the final bout of any session is not in target zone 4, they are advised to adjust their wall-squat position up or down by 1 cm to maintain optimum training intensity going forward. To check fidelity of the intervention early on in the study an interim analysis of RPE recorded at the last bout of the first 3 exercise sessions for the first 50 participants in the intervention arm will be conducted.

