### Participant on study timeline and assessments

This section describes the assessments and visits conducted with participants once they are randomised.
Table 1 overleaf summarises the schedule of assessments at each time point and
Figure 2 provides a flow chart of participant flow through the study. There are no prohibited interventions during the trial. Participants’ (control and intervention) GP’s or other relevant healthcare organisation (e.g. hospital) will continue to be responsible for normal care provision with respect to hypertension and other medical conditions through and post study participation. A letter will be sent to the participant’s GP to inform them of participation in the study and what that involves. Participants will be able to request a copy of this. Participants will be advised to seek advice and care from their GP throughout the study should their condition change. Participants will be asked not to alter medication unless absolutely necessary and after consultation with their GP. Participants with BP > 180/120 will be advised to seek urgent medical review, GPs will be advised to follow NICE guidelines in relation to urgent specialist referral.

**Table 1. T1:** Participant schedule of assessments.

Assessment	Pre- screening	Screening	Baseline Day 1 (start date of IE training)	Follow up 1 Day 30 (+/− 3 days)	Follow up 2 Month 3 (+/− 7 days)	Follow up 3 Month 6 (+/− 7 days)	Follow up 4 ^ 1 ^ Month 12 (+/− 7 days)
Pre-screening form	X						
Collection of unidentified demographic data	X						
Consent		X					
Home BP readings		X ^ 2 ^	X ^ 3 ^	X	X	X	X
Confirmed IE ability		X					
Randomisation			X				
Standard Care lifestyle advice			X				
Self-prescribing of IE ^ 4 ^			X				
Outside range RPE data ^ 5 ^				X			
Diet questionnaire			X		X	X	X
Concomitant medication			X	X	X	X	X
Exercise questionnaire			X		X	X	X
Quality of life questionnaire			X		X	X	
IE experience questionnaire				X			
Health resource use questionnaire					X	X	
Invitation to take part in study focus group				X			

1 – first n=50 invited and accepting to continue follow up until Month 12 2 - recorded between Day -7 and Day 0 3 - if Screening BP measures ≥28 days prior to baseline 4 - IE group only 5 – collected from the first n=50 participants only for fidelity assessment

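### The fidelity outcome is defined on fourth-bout RPE in the first three sessions, but the data described for it are confirmations with no session named, scheduled once at Day 30

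*Protocol article*

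**What the plan says.** The protocol article describes the fidelity measure in five places.

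- **Isometric Exercise Training (text after Figure 3):** to check fidelity early in the study there will be "an interim analysis of RPE recorded at the last bout of the first 3 exercise sessions for the first 50 participants" of the intervention arm. The same text tells participants to move their squat position by 1 cm whenever the final bout is not in target zone 4.
- **Statistical methods, list of secondary outcomes:** fidelity is to be shown by "RPE recorded in range at the last bout for the first week of training", again in the first 50 intervention participants.
- **Statistical methods, quantitative data analysis:** the interim analysis concerns "fourth bout RPE scores and the extent to which these are in range of the target zone". The next sentence states what is collected: "Data collected for this purpose involves confirmation from participants on whether they altered their wall squat height and whether their RPE was outside of range".
- **Follow up assessments:** the same two items are named, out-of-range RPE and the need to alter the wall squat, in the first 50 intervention participants.
- **Table 1:** the row "Outside range RPE data" has one mark, under Follow up 1 (Day 30 +/- 3 days). A footnote limits it to the first 50 participants.

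One further sentence bears on data entry. The Follow up assessments section says that "reminders will include a link to input their data each time or at regular weekly intervals", without saying what is entered.

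**The concern.** An outcome built on recorded scores in a fixed early window needs those scores, or at least an in-range flag, for each session in that window. The article says what will be collected, and it is something else: confirmations tied to no session, placed in the schedule some three weeks after the sessions they should describe.

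The exercise is self-prescribed at home, and this is the only analysis of training intensity that the article describes. If the data are collected as written, the team may reach the analysis with answers that do not map onto the stated outcome and would have to redefine it afterwards.

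The height item adds a difficulty of its own. The first session is where participants find their position, and they are told to adjust later if the final bout misses the zone. A report that the height was altered may therefore show that the instructions were followed, not that fidelity failed.

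**Working it through.** The article gives no target, threshold or precision for fidelity, so there is no figure to reproduce. The check compares the places in the text and then asks what each possible form of the data could deliver.

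**1. The places side by side**

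| Place | Unit | Sessions covered | When collected |
|---|---|---|---|
| Isometric Exercise Training | RPE recorded at last bout | First 3 sessions | Not stated |
| Secondary outcomes | RPE in range at last bout | First week | Not stated |
| Quantitative analysis, first sentence | Fourth-bout RPE scores | Not stated | Not stated |
| Quantitative analysis, next sentence | Confirmation: out of range; height altered | Not stated | Not stated |
| Follow up assessments | Whether out of range; whether alteration required | Not stated | Not stated |
| Table 1 | Out-of-range RPE data | Not stated | Day 30 +/- 3, once |

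At three sessions a week, the first three sessions and the first week are the same window, so the first two rows agree. The unit changes from score to confirmation within one paragraph of the analysis section. The scheduled time is 30 - 7 = 23 days after the end of the first week, or 20 to 26 days with the visit window.

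**2. What each form of the data could give**

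Inputs: N = 50 participants (article) and s = 3 sessions in the window (article), so N x s = 150 sessions. Let y be the number of participants who answer that RPE was out of range. Assume that everyone completes the three sessions and answers correctly.

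- *(a) One confirmation per session for the first three sessions.* In-range proportion = 1 - (out-of-range sessions)/150. It is known exactly, but there are no scores and no distance from the zone.
- *(b) One answer per participant about the first week.* Each yes stands for 1, 2 or 3 out-of-range sessions. Lower bound = 1 - 3y/150; upper bound = 1 - y/150. The participant-level proportion never out of range, 1 - y/50, is exact.
- *(c) One answer per participant covering all sessions to Day 30* (3 x 30/7 = 12.9, so about 12 to 13 sessions). The out-of-range sessions may all fall after the first week, so the upper bound becomes 100%. The lower bound is unchanged.

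| Yes answers (illustrative) | (b) first-week window | (c) all sessions to Day 30 |
|---|---|---|
| 10 of 50 | 1 - 30/150 = 80.0% to 1 - 10/150 = 93.3% | 80.0% to 100% |
| 25 of 50 | 1 - 75/150 = 50.0% to 1 - 25/150 = 83.3% | 50.0% to 100% |

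These bounds need no assumption that sessions are independent. Independence would fit poorly here, because participants are told to change position after an out-of-range final bout.

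The article does not say whether (a), (b) or (c) applies. Only (a) gives the session-level in-range proportion, and none of the three gives scores.

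**The case against.** A reader might infer that yes/no data can never give the in-range proportion. That goes too far. The listed outcome is itself an in-range/out-of-range measure, and a confirmation that RPE was out of range is its complement. Answers per session for the first week would give the proportion directly, and one first-week answer per person would give a participant-level proportion.

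Nor does the article say that there is a single recalled item or a window running to Day 30. It speaks of RPE being recorded, and it mentions links for entering data at each session or weekly. Table 1 has no column between Baseline and Day 30, so the mark may show when first-week records are submitted. Early in the study may mean early in the trial, in which case Day-30 data from the first 50 of 271 planned intervention participants are still early. The exact questions belong to the data collection tools, which the article places in its repository and which are not shown here.

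All of this stands, and it limits the point. It does not remove it. The article states both the outcome and the data for it, and the two differ. Unseen forms may settle the matter in practice, but the text does not say that RPE is entered through the session links, and no analysis plan can recover scores that were not collected.

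**Conclusion.** The point holds in a limited form. The unit, the sessions covered and the collection time of the fidelity measure do not agree across the article. Data collected as described would not give the scores that the analysis names and would not ensure the first-week in-range proportion that the outcome requires.

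The size depends on an assumption. If there is one answer per participant, 25 of 50 positive answers leave session-level fidelity between 50% and 83% for a first-week window, and between 50% and 100% for a window to Day 30. If confirmations are recorded for each of the first three sessions, the proportion is not lost at all; only the scores are.

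A reader might also infer that the mismatch would stop a null trial from being explained. The documents do not support that. This is a first-week process measure in 50 people, and even perfect data on it could not separate failed delivery from an ineffective exercise at three months. No stopping rule and no part of the primary analysis is stated to depend on it. The change is worth making because a listed secondary outcome and its stated data do not match, and because it is cheap.

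**What to change.** For the first 50 intervention participants, collect the fourth-bout RPE score and any change of squat height for each of the first three sessions, entered at the session. The existing reminder links could carry this. Define the outcome as the proportion of those sessions in the article's own target zone. Report height changes separately and descriptively, since an adjustment may be correct use of the instructions.

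Then align the Isometric Exercise Training text, the Follow up assessments text, Table 1, the secondary outcome list and the quantitative analysis paragraph on unit, sessions and collection time.

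At minimum, keep the yes/no item but record it per session for the first three sessions, redefine the outcome on it, and remove the reference to analysing scores.

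The cost is three short online entries for 50 people who already rate their exertion at every session, a change to the REDCap form, and edits to the text and Table 1.
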